### Randomization

2.5

To randomly assign participants to the experimental groups, a 40-number draw (34 patients + 20% of drop out, if need be) will be conducted using the Microsoft Excel 2017 version program. The distribution of the groups will be identical (1: 1) for both groups. Distribution will be performed in a blocked manner (5 groups of 8 patients). Opaque envelopes will be identified with sequential numbers (1 to 40) and inside there will be information from the corresponding experimental group according to the order obtained in the draw. The envelopes will be sealed and remain sealed in numerical order until the time of mini-implant placement and laser application. The draw and preparation of the envelopes will be performed by a person not involved in the study. Immediately before the laser application, the treating researcher will open 1 envelope (without changing the number sequence) and perform the indicated procedure. Three additional patients will be included in each group due to the drop out predicted in every clinical study (considering a 20% drop out). The author of the research will be responsible for the storage (digital platforms) and tabulation of information, being the statistician responsible for analyzing the data obtained at the end of the research. These same envelopes will contain the patient records (with anamnesis sheet, ICF and radiographs) and will be kept on file.

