## Methods

2

This is a prospective, single-center, randomized, controlled, double-blind, 90-day follow-up trial that meets the criteria for a SPIRIT Statement clinical trial design. This protocol received approval from the Human Research Ethics Committee of *Universidade Nove de Julho* (certificate number: 3 533 219). Any complications or alterations will be reported and clarified to REC and reported in the publications. After verbal and written explanation of the study ([name]), patients who agree to participate in the study will sign the Informed Consent Form (ICF). If patients want to receive the research data, they can put the e-mail in the informed consent form and the full article can be checked as soon as it is published. The study will be conducted in accordance with the Helsinki Declaration (revised Fortaleza, 2013). The Project was registered at www.clinicaltrial.gov with NCT 04037709. The patients will come from [name]'s office and staff, located at [name]. There is no conflict of interest with regard to the clinics where the research will be conducted and with respect to any product used at work and with respect to any author involved in the study. Project receive grant from Brazilian National Coordination for the Improvement of Higher Education Personnel CAPES #690822 (CAPES Portuguese: Coordenação de Aperfeiçoamento de Pessoal de Nível Superior (CAPES).

The sample will consist of adult patients, who live in the city of São Paulo, Brazil, and who require lower molar verticalization for prosthetic rehabilitation. The description will be detailed in the item “Orthodontic verticalization mechanic and placement of the mini-implant”. The experimental design will consist of 2 groups (will be described in detail in the item “Experimental Design”). Samples will be collected for evaluation of inflammatory cytokines of crevicular gingival fluid. The intensity of pain will also be evaluated through the visual analog scale, the amount of medication taken and the vertical velocity of both groups. An OHIP-14 questionnaire will also be applied to measure oral health-related quality of life (Fig. 1  flowchart). Data will be published and there will be no restriction on including data for publication. All data will be available for consultation, and all patients will have access to their records at any time.

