### Study blinding

2.6

Only 1 external research collaborator, with dental training, who will be responsible for the treatments (which will open the envelopes of randomization), will know which photobiomodulation treatment will be assigned to each patient. The identification of each group will be revealed by this collaborator to all involved only after statistical analysis of the data. Therefore, the researcher responsible for data collection and the statistician will be blinded to the treatments assigned to the groups. The patient will also be blind to the type of treatment performed, since the mini-implant placement treatment will be identical in both groups and the laser treatment for photobiomodulation will be simulated in the control group.

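### A published fixed block of 8, with one unblinded treating researcher opening every envelope in order, makes on average 8 of 40 allocations predictable to that person and weakens concealment

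*Protocol article*

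**What the plan says.** The opening of the Methods states: "This is a prospective, single-center, randomized, controlled, double-blind, 90-day follow-up trial". Section 2.5 sets up "a 40-number draw (34 patients + 20% of drop out, if need be"), with equal allocation ("The distribution of the groups will be identical (1: 1) for both groups"), and then fixes the restriction: "Distribution will be performed in a blocked manner (5 groups of 8 patients"). No stratification is mentioned, so there is a single sequence.

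At the point of use, section 2.5 says that "the treating researcher will open 1 envelope (without changing the number sequence) and perform the indicated procedure". Section 2.6 describes one external collaborator "who will be responsible for the treatments (which will open the envelopes of randomization), will know which photobiomodulation treatment will be assigned to each patient". Section 2.12 confirms that only the person applying the laser knows the groups.

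The same sections also give safeguards. Someone outside the study makes the draw and prepares the envelopes, which are opaque, numbered and sealed. They are opened immediately before the laser application. Under section 2.7, consent, OHIP-14, crevicular fluid and VAS come before the randomised treatment, and a different researcher collects the baseline data. Section 2.2 keeps that researcher out of the treatment of patients. Section 2.6 blinds the data collector and the statistician.

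**The concern.** Opaque sealed envelopes stop someone from reading the next assignment. They do not stop someone from deducing it. In a block of known size, once one arm has used up its places, the rest of the block is certain. Before that point, the arm with fewer patients so far is the better guess. The person best placed to deduce this is the one who has seen every past assignment, and here the same person is about to treat the next patient.

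The late opening of the envelope is meant to keep the steps before the laser independent of the arm. Some of those steps involve judgement. Eligibility in section 2.4 includes a favourable periodontal condition, and section 2.11 bases the mini-implant dimensions on the radiograph and the cortical bone. The primary outcome is the change in molar angle over 90 days, which could depend on who is treated and on how the mechanics are set up. A blinded reader of the radiographs cannot remove a difference that entered at that stage, and with 17 patients per arm a few influenced cases could matter.

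**Working it through.** **Inputs.** Block size 8, five blocks, 1:1 and 40 envelopes (section 2.5); 34 patients planned, with the reserve used only if needed (sections 2.1 and 2.5). The article does not state 4 + 4 within each block; this is inferred from 1:1. It gives no predictability figure. Its list length is consistent with its blocks: 5 × 8 = 40.

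**Deducible assignments.** Let m be the number per arm in a block of 2m. An assignment is certain once the other arm has reached m, so the number of certain assignments equals the length of the final run. Its mean is 2m/(m + 1).
- For m = 4: 8/5 = 1.6 per block.
- Enumerating all C(8,4) = 70 orders gives 1, 2, 3 or 4 certain assignments in 40, 20, 8 and 2 orders: (40 × 1 + 20 × 2 + 8 × 3 + 2 × 4)/70 = 112/70 = 1.6.
- All 40 envelopes: 5 × 1.6 = 8.0 (20%).
- Only 34 envelopes, which is four full blocks and two of the fifth: 4 × 1.6 = 6.4 (19%). Two envelopes cannot exhaust an arm of four, so the fifth block adds none.

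**Correct guesses from a tally.** Guess the arm with more places left and toss a coin when level. The expected number correct in a block is m + (4^m / C(2m, m) − 1)/2. For m = 4: 4 + (256/70 − 1)/2 = 5.33 of 8, or 66.6%. Enumeration gives the same.

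**Alternatives, per 40 patients.** The certain assignments in this table suppose that the block size is known.

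| Block size | Certain | Correct guesses |
|---|---|---|
| 2 | 20.0 | 75.0% |
| 4 | 13.3 | 70.8% |
| 6 | 10.0 | 68.3% |
| 8 (plan) | 8.0 | 66.6% |
| one list of 20 + 20 | 1.9 | 58.7% |

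For the last row: 40/21 = 1.9, and 20 + (4^20 / C(40,20) − 1)/2 = 20 + (7.976 − 1)/2 = 23.49 of 40.

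**Why small mixed blocks are a poor remedy.** The tally returns to level at the end of each block whatever its size, so this guess does not need the block sizes. An undisclosed mix of 2, 4 and 6 (assuming 3, 4 and 3 blocks, total 40) gives 3 × 1.5 + 4 × 2.833 + 3 × 4.1 = 28.1 of 40, or 70.3%. It removes most of the certainty but raises guessing above the present 66.6%.

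**Balance if recruitment stops at 34.** Under the plan, the two envelopes from block 5 differ with probability 4/7, giving 17/17; otherwise the split is 18/16. With one permuted list of 40, the variance of one arm's count is 34 × ½ × ½ × (40 − 34)/(40 − 1) = 1.31, so the SD is about 1.1 patients.

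**The case against.** A reader might infer that concealment fails outright, or that 8 patients' allocations are known in advance. The documents do not support this. The figure of 8 is an expectation for an opener who knows the block size and keeps a tally, and the article states neither. The next assignment is predictable to one person only. The independent list-maker, the sealed opaque envelopes and the late opening are proper safeguards.

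A reader might also infer that the opener can steer who is enrolled or when. No section says that this person screens, consents or schedules patients. The opener is described as an external collaborator responsible for treatments, and baseline data belong to someone else. In a condensed article, silence on who enrols is not evidence that the opener does. Without influence on enrolment, a predictable sequence produces no selection bias.

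The route through the mechanics is also narrower than it may look. Section 2.11 applies 150 g, measured with a tensiometer, in all cases, so the initial force is not left free. It does not name the operator who places the implant; that the opener does so is a reading of sections 2.6 and 2.7. Once an envelope is open, this person knows the arm at the 30-day and 60-day chain changes, whatever the block size. Block prediction therefore adds only the first placement, in a minority of patients, and a new list would not remove the later exposure.

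All of this stands, and it limits the point. It does not answer the point that a fixed, published block size and sequential opening by the unblinded treating person give away some allocations without need, when a less predictable list is available.

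**Conclusion.** The point holds as a weakness in concealment, not a failure of it. On average 8 of 40 allocations (6.4 of 34 if the reserve stays unused) can be deduced with certainty by the envelope opener, and a tally-based guess is right 66.6% of the time. These figures assume 4:4 blocks; the first also needs knowledge of the block size, and both need a record of past assignments. Whether bias in the primary outcome would follow depends on the opener's influence over enrolment or placement, which the article does not describe, so no size can be put on it. The change is worth making because it is cheap.

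**What to change.** Before the first envelope is opened, the person outside the study should replace the five blocks of 8 by one of two options:
- one permuted list of 40 (20 + 20), which is the less predictable; or
- larger, randomly varied blocks that avoid sizes 2 and 4. These remove most of the certainty while the sizes stay undisclosed, but they lower tally guessing only a little. For example, 8, 10, 10 and 12 in random order gives, by the formula above, 5.33 + 2 × 6.53 + 7.72 = 26.1 of 40, or 65.3%.

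In either case, the block structure should not be disclosed to the treating researcher, and the block size should come out of the documents that this person uses. The protocol should also state that the envelope opener has no role in eligibility or booking.

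The cost is one new list and a sentence or two in the protocol, with no extra patients. The downside is looser balance if recruitment stops at 34: with one permuted list, one arm's count has an SD of about 1.1 around 17, against at most 18/16 under the present blocks. That is a small price at this sample size.

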### Calibration of researchers

2.2

For calibration, an examiner, trained in dentistry and specializing in orthodontics, will evaluate 5 panoramic radiographies of inclined molars, which will not be part of the study. Two radiographic evaluations will be made (10 days apart) to check for intra-examiner agreement. The intraclass correlation coefficient (ICC) will be calculated to assess intra-examiner agreement ≥ 0.75 with respect to the measurement of lower molar inclination using pre-established radiographic measurements (described in item “Movement rate”). The evaluation will be performed with millimeter ruler + protractor and this researcher will not be involved in the treatment of patients. The same examiner will be trained to collect crevicular gingival fluid (CGF) for cytokine analysis and data collection for OHIP-14 to maximize reproducibility of evaluations.

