### Orthodontic verticalization mechanic and placement of the mini-implant

2.11

At the first consultation, all patients will be clinically and radiographically evaluated, and a treatment plan will be drawn up. Given the need for molar verticalization, an orthodontic mini-implant (Morelli, Sorocaba, SP, Brazil) will be installed in the retromandibular region (Araújo, 2006). First there will be a local asepsis with 2% chlorhexidine solution (2% aqueous chlorhexidine - Rioquímica) and external asepsis with 0.2% chlorhexidine (0.2% aqueous chlorhexidine - Rioquímica). The site will be anesthetized with a carpule (quinelato), short gingival needle (Unoject - Nova DFL) and the anesthetic of choice will be Mepivacaine + 2% Epinephrine 1 ml (Mepiadre 2% 1: 100000 - Nova DFL). The anesthetic technique used will be the infiltrative (essentially local) at 3 points of the retromolar region (central, buccal and lingual). Once this is done, the region will be pre-drilled by about 4 mm with a spearhead coupled to a manual key (Morelli ). In order to have proper anchorage and primary stability, the dimensions of the mini-implant will be chosen based on panoramic radiography and the amount of cortical bone present in the region.^[42]^ Once the mini-implant has been selected (Morelli, Sorocaba, SP, Brazil), it will be locked into position using a kit-specific digital key (Morelli, Sorocaba, SP, Brazil). Being threaded clockwise until the intramucosal mini-implant is at the gingival level. A simple surgery, where there is no osseointegration of the mini-implant, being inserted only in the cortical bone, being therefore easy to remove, and can be activated (force application) immediately. After installation, a metallic orthodontic lingual button (Morelli, Sorocaba, SP, Brazil) will be glued to the molar mesial face to be verticalized. As the molar is verticalized, this lingual button may be retracted more distally so that the elastic always exerts the proper force (this will be evaluated at each patient return by the calibrated operator). For its installation, molar prophylaxis will be performed with a Robinson brush (Robinson straight CA - Microdont brush) and prophylactic paste (Herjos - Coltene), followed by water irrigation and drying. Once this is done, the dental surface will be conditioned with 37% phosphoric acid (Condac - FGM) for 45 seconds, followed by water irrigation for 15 seconds and subtle air drying from the triple syringe. Next, we have the application of single bond adhesive system (Adper Single Bond 2 - 3M Adhesive) and polymerization (Poly Wireless Curing - Kavo) for 5 seconds. The lingual button will be glued to the inclined molar mesial with orthodontic adhesive (Orthocem - FGM), and a small portion of it will be placed on the lingual button grid and, once it is in position, it will be light cured for 45 seconds. A gray chain elastomeric ligature (Morelli, Sorocaba, SP, Brazil) will attach the head of the mini-implant to the lingual button glued to the molar mesial. A light force of 150 g will be imposed (measured with a tensiometer - Morelli, Sorocaba, SP, Brazil)^[43,44]^ in all cases, regardless of tooth position. This chain elastic will be changed every 30 days for a period of 3 months. After 90 days of the experiment time, the mini-implants will be removed. This procedure involves local anesthesia with Mepivacaine + 2% Epinephrine 1 ml (Mepiadre 2% 1: 100000 - Nova DFL) and the mini-implant will be removed only with the digital key being turned counterclockwise. Since there is no osseointegration, its removal is simple and quick, requiring no incision or suture. Painkillers will be available if there is pain. Removal of the lingual button will be performed using bracket pliers (346R-Zatty Straight Bracket Orthodontic Pliers) and resin removal with high-speed diamond drill bits (FG – Fava flame diamond). After the trial period, for those patients who are interested will be offered the possibility to complete (if this 3 months of research has not been achieved) the full verticalization of this molar (ie the mini-implant and lingual button would not be removed after 90 days and changes of the elastic bandage would occur until the case was finalized), so that they could receive future oral rehabilitation (making it clear to the patient that they would no longer be part of the research, and that any charge resulting from this choice would not fit to the researcher).

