## Discussion

3

The study was characterized as a randomized, double-blind, placebo-controlled trial to minimize measurement bias (also referred to as information, observation or measurement), which is the result of systematic differences in the way data about the event of interest is obtained from the various groups under study.^[50]^

Randomization should be performed in prospective studies comparing the effect of an intervention (prophylactic or therapeutic) with their respective controls. The researcher distributes the intervention at random through randomization; Thus, the experimental and control groups are formed by a random decision process.^[50]^

The term double-blind refers to those trials in which neither the patient nor those responsible for their care and evaluation know what treatment he is receiving. Blinding will be performed by randomization during delivery of envelopes, and the group to which the patient belongs is confidentially informed on the brown envelope. The main reason for introducing a placebo-controlled group is to make patients’ attitudes as similar as possible to those of the treated group.^[50]^

For our study, the calculated sample was based on the “amount of motion x time” variable, following the Kadam, 2010,^[41]^ sample size calculation formula: N = 2 (ZA - Z1-β) 2σ2 / Δ2 reaching a “n” of 34 patients (17 patients in each group), with 20% dropout, totaling 3 more individuals in each group. Research participant dropout is unlikely during treatment because it has the mini-implant installed. Therefore, we limited our study to a 90-day follow up.

Our approach was based on a problem that can be pointed as one of the most recurrent conditions in the population, which is the loss of the permanent lower first molar.^[51,52]^ Of various causes, this situation can result in mesial migration of the second molars,^[53,54]^ affecting even the anterior teeth, with opening of diastemas and midline deviations.^[53,55]^ In such cases it is still common to find infraosseous defects in the mesial of the inclined molar, accompanied by a gingival recession and a reduction of the interradicular space in the distal region.^[1]^

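### Allocation envelopes are reused as patient files holding the radiographs, which leaves an avoidable route to the arm for the film reader and the patient

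*Protocol article*

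**What the plan says.** All references are to the protocol article.

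- **Allocation (section 2.5, Randomization).** "Opaque envelopes will be identified with sequential numbers (1 to 40) and inside there will be information from the corresponding experimental group". On timing: "Immediately before the laser application, the treating researcher will open 1 envelope".
- **Filing (section 2.5).** "These same envelopes will contain the patient records (with anamnesis sheet, ICF and radiographs) and will be kept on file".
- **Discussion (section 3).** The arm is again tied to the envelope: "the group to which the patient belongs is confidentially informed on the brown envelope".
- **Blinding (section 2.6).** One external collaborator gives the treatment and knows the arm. Everyone else learns it after the statistical analysis, and "the researcher responsible for data collection and the statistician will be blinded to the treatments assigned to the groups". The patient is also said to be blind, by means of a simulated laser session.
- **Record access (section 2, Methods).** "all patients will have access to their records at any time".
- **Primary endpoint (sections 2.2 and 2.13).** An examiner measures the molar angle with ruler and protractor on the first and the day-90 panoramic film. The values are entered in the patient's chart. Of this examiner section 2.2 says that "this researcher will not be involved in the treatment of patients".
- **Treatment visits (section 2.11).** On moving the lingual button distally: "this will be evaluated at each patient return by the calibrated operator".

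**The concern.** Blinding here rests on two things: a convincing sham, and the arm being known to one person only. The filing rule weakens the second. It places the raw material of the primary endpoint in the container that carried the arm, while the endpoint is still to be measured.

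The endpoint needs this protection. The reader draws a mandibular line and a tooth axis by hand and reads an angle, so judgement enters each value. The calibration in section 2.2 (five films outside the study, read twice 10 days apart, ICC of at least 0.75) checks that the reader repeats himself or herself. It offers no protection against a shift that depends on knowing the arm. VAS pain, OHIP-14 and analgesic use depend in the same way on the patient not knowing.

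**Working it through.** No figure in the protocol bears on this point, so there is nothing to recompute. The check is to follow one envelope through the plan.

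1. **Before treatment.** The envelope holds the assignment and stays sealed in numerical order (section 2.5). Consent and anamnesis are completed at the pretreatment evaluation (section 2.7).
2. **Day 0.** The treating researcher breaks the seal just before the laser or sham session (sections 2.5 and 2.10). Because the envelope is sealed until then, the consent form, anamnesis sheet and baseline film can go into it only once it has been opened.
3. **Day 0 to day 90.** The envelope is open for about 90 days before the final film, which is taken before the mini-implant is removed (section 2.10). VAS pain and analgesic use are recorded throughout this period, and OHIP-14 at its end.
4. **Day 90.** The final film joins the radiographs. The reader needs both films to obtain the angle and enters the result in the chart (section 2.13).
5. **After analysis.** Only now is the arm to be disclosed (section 2.6).

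Put side by side:

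| Statement | Consequence |
|---|---|
| Assignment is in the envelope (2.5) | The envelope identifies the arm unless the slip is taken out |
| Radiographs and records go in the same envelope (2.5) | Anyone handling the file may meet the slip |
| Reader needs those films (2.2, 2.13) | Possible route for the reader between steps 2 and 5 |
| Patients may see their records at any time (Methods) | Possible route for the patient between steps 2 and 5 |
| Arm disclosed only after analysis (2.6) | Conflicts with both routes |

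A search for a safeguard finds none: no section has the slip removed, resealed or filed apart, or has the films coded or masked before reading. The digital storage in section 2.5 concerns the author's storage and tabulation of information. The same section still puts the radiographs in the envelopes.

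A smaller mismatch lies close by. Section 2.11 gives the repeated judgement on the lingual button to a calibrated operator. The only person whose calibration is described is the examiner in section 2.2, who is kept out of treatment, while section 2.6 makes the unblinded collaborator responsible for treatment. The three sections do not make clear who is meant.

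**The case against.** The strongest reply is that the text shows an opportunity and no more. It does not say that the slip stays in the envelope, that the examiner takes films from it, or that filing comes before measurement. Keeping on file may mean archiving at the end. The Discussion calls the group information confidential, section 2.6 states the intended blinding plainly, and a condensed article may leave the handling of slips to a fuller document. This stands as far as it goes, and it rules out saying that blinding is lost. It does not remove the point, because the shared envelope is a rule the article states and not a detail it omits.

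Three stronger readings are tempting, and the document supports none of them.

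- **That the reader and patients will learn the arm.** A reader might infer this from the shared envelope and the promise of record access. The promise is a general statement of openness. It does not say that patients are handed the allocation envelope.
- **That reading bias could create or cancel the whole planned effect.** This needs an SD for the angle change and a size for the reading shift, and the protocol gives neither. Suppose the stated effect size of 0.40 is in SD units and the SD is 3 to 8 degrees (assumed). The planned effect is then 0.40 × 3 = 1.2 to 0.40 × 8 = 3.2 degrees. An assumed shift of 1 degree would not cancel even the smallest of these, nor would 3 degrees cancel the largest.
- **That the calibrated operator wording is a second leak.** Elsewhere the operator is the person applying the laser (section 2.12), so the phrase may simply mean the treating clinician, whose knowledge of the arm is openly stated. Section 2.11 also sets one measured force for all cases, which narrows discretion. It is an ambiguity to clear up.

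**Conclusion.** The point holds as a conflict between a stated filing rule (section 2.5), sharpened by open record access (Methods), and the stated blinding (section 2.6). It leaves an avoidable route to the arm for the reader of a hand-measured primary endpoint and for patients who report secondary outcomes.

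The shared envelope is certain, since the text says so. Whether it would lead to unblinding depends on two things the text does not settle: that the slip stays in after opening, and that the reader or patient handles the envelope before the analysis. The size of any bias cannot be estimated from the document, and no figure should be attached to it. The change is worth making because the endpoint depends on judgement and the correction is cheap. It does not affect the sample size or the analysis.

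**What to change.** In sections 2.5 and 2.6, and in the Methods sentence on record access, state that:

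- once an envelope is opened, the allocation slip goes into a separate locked file held only by the treating collaborator;
- consent form, anamnesis sheet, chart and radiographs are stored under the study number, with no arm information on or in the folder;
- the examiner receives coded baseline and day-90 films in random order, with the arm masked and, where possible, the visit too (the mini-implant is still in place at the final film, so the visit may be recognisable, but this does not reveal the arm because both groups have one);
- until unblinding, patients may see their records without the arm.

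Separately, reconcile sections 2.2, 2.6 and 2.11 on who the calibrated operator is and whether that person knows the arm. Who should make the treatment decision is for the investigators.

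The cost is a second set of folders, the coding of two films per patient, and a few sentences of text. No new staff are needed.
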